### Timeline

The recruitment began in December 2017, and the intervention period is ending in August 2019. Figure 2 shows the study schedule of enrollment, intervention, and assessments.

**Fig. 2 Fig2:**
[figure not shown]
Study schedules of enrolment, intervention, and assessments. Abbreviation: *TSFE* transalveolar sinus floor elevation

### Data collection and management

The data of the patients will be documented both on notebook and on spreadsheets.

The statistical analysis and result of all evaluation will be performed by two experimenters independently. In order to avoid the potential bias, for a patient who needs to insert multiple implants in the posterior maxilla, only one of the random implants will be evaluated.

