### Objectives and hypotheses

The major goals of the current randomized controlled trial are to compare and evaluate the clinical outcomes of the TSFE with different surgical protocols of patients with moderate insufficient vertical bone height (residual bone height is 3–6 mm).

The primary hypotheses are (1) the modified TSFE could achieve ideal clinical results similar to the traditional TSFE but with less patient discomfort and (2) TSFE with or without bone grafting can achieve ideal clinical results. The implant survival rate, complications, marginal bone remodeling, resonance frequency analysis measurements, and patient-reported outcome (visual analog scale, or VAS) for post-operative discomfort and pain will also be considered.

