### Inclusion criteria

1. The participant must be more than 18 years of age.2. The participant must have lost a single tooth or several teeth in the posterior area of the maxilla, where the tooth/teeth has/have been extracted for more than 3 months.3. The residual bone height of each participant is between 3 and 6 mm.4. The width of the alveolar ridge of each participant must be capable of containing an implant with standard diameter.5. The general and local status of the participant must be deemed suitable for implant placement and sinus floor elevation.6. The participant must be willing to sign an informed consent form and follow the rules in regard to follow-ups of the study.

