### Groups, randomization, and blinding

By means of randomization tables, all patients will be assigned to one the following four groups: (1) TSFE using osteotomes with bone grafting, (2) TSFE using osteotomes without bone grafting, (3) modified TSFE with bone grafting, or (4) modified TSFE without bone grafting. To ensure the blinding, the surgeon will not partake in the statistical analysis. On the other hand, the surgical plan and grouping will be confidential to the statistical analyst. Figure 1 shows the flow of participants through the trial.

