### Examination during the follow-ups

#### Follow-up plan

All patients will be recalled for a follow-up session at weeks 2, 6, 8, 12, 16, 26, and 52 after the surgery. For each session, the implant and its supra-structure and mucosa around the implant will be examined. The implant stability will be examined at weeks 6 8, 12, 16, and 26 after the surgery. For weeks 26 and 52 after the surgery, the peri-apical radiographic examinations will be performed to record the hard tissue and bone substitute alterations around the implant. For standardization, the paralleling technique with a rinnfilm holder (XCP Instruments; Rinn Corporation, Elgin, IL, USA) will be applied. Surgical complications, which include infection, hematoma, nasal bleeding, nasal obstruction, and benign paroxysmal positional vertigo (BPPV), will be documented. Any complications of implant and its supra-structure will be documented. Besides, patients will finish a VAS scale to evaluate pain, swelling, and bleeding during the first two weeks after surgery.

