### Secondary parameters

The secondary parameters of this study include the following:1. VAS scale to evaluate pain, swelling, or bleeding after the surgery or a combination of these.2. Complications during and after the surgery which including infection, hematoma, nasal bleeding, and BPPV.3. Mucosal condition around the implant: The parameters include depth of probing, sulcus bleeding (by modified sulcus bleeding index), plaque around the restorations (by modified plaque index) will be documented. And the occurrence of biological complications (peri-implantitis and peri-implant mucositis) will be recorded.

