### Statistical analysis

For any continuous data (such as residual bone height or marginal bone remodeling), the inter-examiner agreement between the two examiners will be tested by the intra-class correlation coefficient. For the descriptive data, the inter-examiner agreement will be tested by the Cohen’s κ statistics.

The descriptive data will be expressed in absolute or relative percentage forms, and differences between the two subgroups will be analyzed by chi-squared test. The continuous data will be represented by mean and standard deviations, and the difference between the groups will be tested by analysis of variance (ANOVA).

In order to avoid the interference of measurement metrics due to having two main factors (surgical methods and bone grafting) in the current study, groups that are identical on individual aspects will be combined to discover the influence on the primary results by surgical method and bone grafting, respectively. For the surgical methods, results will be compared between the combined groups 1 + 2 and 3 + 4, whereas for the bone grafting, results will be compared between the combined groups 1 + 3 and 2 + 4. The difference between the groups will be tested by unpaired *t* test.

The statistical significance difference will be set as a *P* value of less than 0.05. All data analyses will be performed by SPSS statistical software .

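### The one-implant rule cannot reach the patient-reported VAS; adjusting that comparison for the planned number of implants would be a nearly free gain in precision

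*Protocol article*

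**What the plan says.** All references are to the protocol article.

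- **Eligibility** (Inclusion criteria): "The participant must have lost a single tooth or several teeth in the posterior area of the maxilla". The number of implants can therefore differ between patients.
- **Multi-implant patients** (Data collection and management): to avoid potential bias, "for a patient who needs to insert multiple implants in the posterior maxilla, only one of the random implants will be evaluated".
- **VAS** (Follow-up plan): "patients will finish a VAS scale to evaluate pain, swelling, and bleeding during the first two weeks after surgery". The abstract also mentions a VAS for intraoperative discomfort.
- **Status of the VAS**: the Secondary parameters section lists it as "VAS scale to evaluate pain, swelling, or bleeding after the surgery or a combination of these". Yet the first primary hypothesis (Objectives and hypotheses) is that "the modified TSFE could achieve ideal clinical results similar to the traditional TSFE but with less patient discomfort".
- **Analysis** (Statistical analysis): for continuous data, "the difference between the groups will be tested by analysis of variance (ANOVA"). A further unpaired t test is described in which "groups that are identical on individual aspects will be combined to discover the influence on the primary results". No covariate is named for either test.
- **Allocation** (Groups, randomization, and blinding): "By means of randomization tables, all patients will be assigned to one the following four groups". No stratification by number of implants is stated.

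**The concern.** The article itself treats patients with several implants as a possible source of bias, and its only remedy is to evaluate one implant chosen at random. Selecting an implant changes which survival, stability or bone measurement enters the analysis. It changes nothing about a pain or swelling score, because a patient cannot report these for one site only. If several sites are treated in one operation, the score reflects all of them. Extent of surgery is then a plausible source of VAS variation, and the stated test leaves it in the error term.

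At stake is the precision of the discomfort comparison. The VAS is formally secondary, but less discomfort is the advantage claimed for the modified technique in the first primary hypothesis.

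**Working it through.** **The plan's own figure.** The Sample size section plans 27 per group before dropout, for bone remodeling (difference 0.8 mm, SD 1 mm, α 0.05, power 90%). With a one-sided α, n = 2 × (1.645 + 1.282)² × 1² / 0.8² = 26.8, so 27, and 27 / 0.9 = 30. (A two-sided α would give 33, but that is a separate matter.) This calculation does not cover the VAS, for which the article gives no difference, SD or sample size. It is used here only for n = 2 × 27 = 54 per technique.

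**Inputs not in the documents, so assumed.** p is the share of patients with two or more implants, taken as 0.1 to 0.5. g is their mean VAS excess over single-implant patients, in within-stratum SD units, taken as 0.25 to 1.0.

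**Formula.** With the within-stratum variance set to 1, the VAS variance within an arm is v = 1 + p(1−p)g² if implant number is ignored. So:
- the standard error is larger by the factor √v;
- the share of variance explained by implant number is 1 − 1/v;
- adjusting is worth as much as p(1−p)g² more patients.

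The last column is the two-sided power of the unadjusted test when the adjusted test has 80%.

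| p | g | v | SE increase | Variance explained | Power |
|---|---|---|---|---|---|
| 0.1 | 0.25 | 1.0056 | 0.3% | 0.6% | 79.8% |
| 0.2 | 0.5 | 1.0400 | 2.0% | 3.8% | 78.4% |
| 0.3 | 0.5 | 1.0525 | 2.6% | 5.0% | 78.0% |
| 0.5 | 0.5 | 1.0625 | 3.1% | 5.9% | 77.6% |
| 0.3 | 0.8 | 1.1344 | 6.5% | 11.8% | 74.9% |
| 0.3 | 1.0 | 1.2100 | 10.0% | 17.4% | 72.1% |
| 0.5 | 1.0 | 1.2500 | 11.8% | 20.0% | 70.7% |

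With p = 0 or g = 0, v = 1 and nothing is lost. The factor √v does not depend on n, so the SE increase is the same for two single arms as for pooled arms.

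**Chance imbalance is the same loss.** With n per side, the share of multi-implant patients differs by chance between the sides with SD √(2p(1−p)/n). This moves the VAS contrast by g times that amount. The variance of the unadjusted contrast is (2/n) × [1 + p(1−p)g²] = 2/n + g² × 2p(1−p)/n, and the second term is exactly the variance of that shift.

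Example with n = 54, p = 0.3, g = 0.5:
- The imbalance SD is √(0.42/54) = 0.088, and the shift SD is 0.5 × 0.088 = 0.044.
- The contrast variance is 2/54 + 0.044² = 0.0370 + 0.0019 = 0.0390, so the SE is 0.197.
- The adjusted SE is √(2/54) = 0.192. The ratio is 1.026, which is the 2.6% in the table.

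**The case against.** The strongest reply is that nothing in the plan is wrong. The one-implant rule does its job for the three primary parameters, and the article never says that it governs the VAS. Each patient contributes one VAS report at a given assessment, so there is no within-patient clustering over implants to repair. Allocation is random by patient, and the number of implants needed precedes treatment, so leaving it out causes no systematic bias. Covariate adjustment of a secondary outcome is commonly left to an analysis plan, and none is shown. The same remark could be made about age or residual bone height. The size rests on two quantities that the documents do not give.

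Most of this stands. A reader might infer that the VAS comparison is biased by multi-implant patients, or that implants are wrongly counted as independent. The documents support neither. A reader might also count a chance imbalance in multi-implant patients as a second harm. As shown above, it is the same variance counted again. Nor should the pooled t test be presented as the planned VAS analysis: it is described for the primary results, and the VAS falls under the ANOVA sentence. That all implants go in at one operation, each with its own elevation, is inferred and not stated.

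What the reply does not remove is narrower. The article names multi-implant patients as a problem, its remedy cannot act on one outcome in its first hypothesis, and the stated test for that outcome takes no account of them. This variable differs from other possible covariates because the one-implant rule already requires knowing which patients need several implants.

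**Conclusion.** The point holds as a small, optional gain in efficiency. The stated ANOVA of the VAS is valid and unbiased but may be less precise than it need be. If 10% to 50% of patients need several implants and their VAS is 0.25 to 1.0 within-stratum SD higher, the standard error is about 0.3% to 12% larger than with adjustment. At 0.5 SD and 20% to 50% of patients it is 2% to 3% larger, which turns 80% power into about 78%. The loss is zero if implant number does not affect VAS, and negligible if few patients need several implants. These ranges are assumptions, and they also suppose that the implants are placed in one operation. The primary parameters are not affected.

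**What to change.** State that the one-implant rule applies to implant-level outcomes only. For the VAS outcomes, replace the ANOVA by a linear model with technique, grafting and the planned number of posterior-maxilla implants (1 versus 2 or more). The technique coefficient then addresses the discomfort part of the first hypothesis directly.

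Take the number from the pre-surgical plan, recorded before allocation is known, and not from what was finally placed. The number placed can depend on what happens during the operation, whereas the planned number remains a baseline variable.

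The cost is a sentence or two of analysis wording and one model term. With 4 × 27 = 108 evaluable patients and four coefficients including the intercept, 104 residual degrees of freedom remain, so little is lost even if implant number proves irrelevant. No extra patients or visits are needed.

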### Primary parameters of the trial

The primary parameters of the current trial are implant survival rate, implant stability, and the bone remodeling around the implant.

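### The one-random-implant rule makes no exception for implant loss or peri-implant disease, so read literally it understates how many patients have such an event

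*Protocol article*

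**What the plan says.** All references are to the protocol article.

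- **Inclusion criteria** admit multi-tooth gaps: "The participant must have lost a single tooth or several teeth in the posterior area of the maxilla". Neither the expected share of such patients nor the number of implants each may receive is stated.
- **Data collection and management** sets the unit of evaluation when a patient receives several implants in this region: "only one of the random implants will be evaluated". The reason given is "In order to avoid the potential bias". The sentence before it concerns the analysis and results of all evaluation, and no outcome is exempted.
- **Primary parameters of the trial** names three outcomes: "The primary parameters of the current trial are implant survival rate, implant stability, and the bone remodeling around the implant". Survival is therefore a primary outcome here.
- **Secondary parameters**, on peri-implant disease: "the occurrence of biological complications (peri-implantitis and peri-implant mucositis) will be recorded".
- **Follow-up plan**: "Any complications of implant and its supra-structure will be documented". Surgical complications are listed separately: "Surgical complications, which include infection, hematoma, nasal bleeding, nasal obstruction, and benign paroxysmal positional vertigo (BPPV), will be documented". The section refers to the implant in the singular and does not say whether unselected implants are covered.

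**The concern.** The one-implant rule is a sound way to avoid clustered observations when arms are compared on implant-level measurements. It is less suited to counting harm. A patient may keep the selected implant and lose a neighbouring one placed with the same allocated technique. Taken at its word, the rule enters that patient as a survivor without an event. The Missing data section makes the contrast sharper: a dropout counts as a non-survival, whereas a known loss at an unselected implant counts for nothing.

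What is at stake is the number of patients with at least one implant loss or peri-implant complication. Such events may be few in a trial of 120 patients, so each one omitted matters for description. The Discussion says the trial is to explore whether the modified technique brings fewer complications, and a count of affected patients is part of that picture.

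**Working it through.** The plan gives no figure on this point to reproduce. The only input from the documents is the total of 4 × 30 = 120 patients (Sample size). Implants per patient and event rates are not given, so everything in steps 3 and 4 rests on assumptions.

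**1. Do the passages fit together?** Two readings are possible.
- The follow-up plan covers all implants. Events at unselected implants are then documented, but the evaluation rule gives them no stated place in the results.
- The follow-up plan covers only the selected implant, as its singular wording allows. The events are then not captured at all.

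Under either reading they are absent from the reported results as the text stands.

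**2. Chance of missing an event.** If exactly one of k implants has the event and one implant is selected at random, P(missed) = 1 − 1/k.
- k = 2: 1 − 1/2 = 50%.
- k = 3: 1 − 1/3 = 67%.

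This needs no assumption about event rates. It does assume a single event in the patient. If j of k implants are affected, the patient is missed with probability 1 − j/k, which is zero when all fail together.

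**3. Share of implants outside the evaluation.** Let q be the share of patients with m implants, all others having one. Unevaluated implants = 120 × q × (m − 1). Implants placed = 120 × (1 − q + qm).

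| q (assumed) | m (assumed) | Unevaluated | Placed | Share |
|---|---|---|---|---|
| 10% | 2 | 12 | 132 | 9% |
| 30% | 2 | 36 | 156 | 23% |
| 50% | 2 | 60 | 180 | 33% |
| 50% | 3 | 120 | 240 | 50% |

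At an assumed loss rate of 2% to 10% per implant, the uncounted losses run from 12 × 0.02 = 0.24 to 120 × 0.10 = 12. The range is too wide to support any single figure.

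**4. Implant rate against patient count, one example.** Assume q = 50%, m = 2 and a 5% loss rate per implant.
- Expected losses among all implants: 180 × 0.05 = 9. Among selected implants: 120 × 0.05 = 6.
- The selected-implant rate stays at 6/120 = 5%, so it is not biased.
- Expected patients with any loss, if losses within a patient are independent: 60 × 0.05 + 60 × (1 − 0.95²) = 3 + 5.85 = 8.85, against 6 counted.
- If losses within a patient always occur together, 6 patients are affected and all 6 are counted.

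The understatement therefore concerns the count of affected patients. It shrinks as within-patient clustering grows.

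**The case against.** The strongest reply is that this is a unit-of-analysis rule. The word *evaluated* follows a sentence about statistical analysis, the stated purpose is to avoid bias, and documentation of complications is dealt with separately. The passages can be read as compatible: document every complication, and compare arms on one implant per patient. The full protocol or case-report form may list every implant.

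Much of this stands, and it rules out several stronger readings that a reader might infer:

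- **That events at other implants are deliberately discarded.** The text does not say so. It leaves the question open.
- **That the comparison between arms is biased.** It is not. Selection is random, the rule is the same in all four groups, and the per-implant rate is preserved.
- **That the trial's safety results as a whole are affected.** Implant survival is a primary parameter here. Pain and swelling scores, hematoma, nasal bleeding and vertigo are mainly patient-level outcomes and the rule does not remove them.
- **That every other implant had the allocated sinus lift.** The documents do not say this. Some neighbouring sites may have needed no elevation, and failures there should not be attributed to the technique.

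The reply does not supply a route into the results for events at unselected implants. Independence does not require leaving them out either, since any event per patient is also one observation per patient.

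**Conclusion.** The point holds as a gap in what is counted and reported. The rule on evaluating one implant carries no exception for loss or biological complications, and the follow-up plan does not settle whether unselected implants are covered. Read literally, the number of patients with a loss or peri-implant disease is understated.

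The firm figure is conditional: a single event among two implants is missed with probability 50%, and among three with probability 67%. A reader might want to quote a trial-wide share, such as 23% or 33%. Those values depend wholly on an assumed proportion of two-implant patients, and the documents give no basis for choosing one. If few patients receive more than one implant, the effect is negligible.

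The correction is worth making because it is cheap. The randomised comparisons of survival, stability and bone remodeling at the selected implant do not depend on it.

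**What to change.** In Data collection and management, confine the one-implant rule to the stability and bone-remodeling comparisons and to the selected-implant survival rate.

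In addition, state there and in the Follow-up plan that implant loss, peri-implantitis, peri-implant mucositis and supra-structure complications are recorded for every implant placed under the allocated sinus-lift procedure. Report them per patient, as any event, alongside the selected-implant result. Implants placed without the allocated lift stay outside this count.

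The sample size does not change, because each analysis still has one observation per patient. The cost is a few more case-report lines, at visits these patients already attend, and event rates that may look slightly less favourable. Adjusting pain scores and surgical complications for the number of implants is optional and not part of this correction.

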### Statistical analysis

For any continuous data (such as residual bone height or marginal bone remodeling), the inter-examiner agreement between the two examiners will be tested by the intra-class correlation coefficient. For the descriptive data, the inter-examiner agreement will be tested by the Cohen’s κ statistics.

The descriptive data will be expressed in absolute or relative percentage forms, and differences between the two subgroups will be analyzed by chi-squared test. The continuous data will be represented by mean and standard deviations, and the difference between the groups will be tested by analysis of variance (ANOVA).

In order to avoid the interference of measurement metrics due to having two main factors (surgical methods and bone grafting) in the current study, groups that are identical on individual aspects will be combined to discover the influence on the primary results by surgical method and bone grafting, respectively. For the surgical methods, results will be compared between the combined groups 1 + 2 and 3 + 4, whereas for the bone grafting, results will be compared between the combined groups 1 + 3 and 2 + 4. The difference between the groups will be tested by unpaired *t* test.

The statistical significance difference will be set as a *P* value of less than 0.05. All data analyses will be performed by SPSS statistical software .

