## Methods/Design

### Overview

The proposed study is designed as a prospective single-center, four-arm parallel group, randomized controlled trial. We plan to recruit 120 patients who are in need of dental implant treatment in the atrophied posterior maxilla. The participants will be recruited by the research staff from Peking University Hospital of Stomatology First Clinical Division (Beijing, China). All interventions, follow-ups, and assessments will also be performed at this location. The study has been approved by the ethics committee of the Peking University School and Hospital of Stomatology (PKUSSIRB-201733019). The study has been registered in ClinicalTrials.gov under identifier number NCT03445039.

The systemic health condition and oral health condition of all participants will be recorded and inspected prior to surgery. All patients joining the study will receive standard oral hygiene maintenance instructions before implant surgery. Panoramic and cone beam computed tomography (CT) scan will be taken to assess the initial bone height, bone quality, and bone width.

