### Sample size

The sample size of the current trial is calculated based on the formula: *n* = 2(t_α_ + t_1-β_)^2^σ^2^/δ^2^. According to the preliminary experiment results and data analysis from currently published articles, the difference of the bone remodeling with and without bone grafting groups (δ) is around 0.8 mm, the difference of the bone remodeling between the original TSFE groups and modified TSFE groups is around 0.5 mm, and the standard deviation in groups (σ) is around 1 mm.

Thus, if the inspection level (α) is set at 0.05 and the power of test (β) is set at 90%, then 27 participants will be required for each group. Given a loss to follow-up rate of around 10%, the study would be anticipated to require 30 participants for each group. As a result, this trial will require at least 120 participants in its current setup.

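### Collapsing the 2×2 design into two unpaired t tests leaves the other factor in the error term and costs the technique comparison about 6 points of power

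*Protocol article*

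**What the plan says.** The trial has four arms formed by crossing technique (osteotome or modified) with grafting (with or without). In the Statistical analysis section, continuous outcomes are to be summarised by mean and SD and compared between groups by ANOVA. No factors, interaction or covariates are named for that ANOVA.

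For the two factor questions the section names a different method: "groups that are identical on individual aspects will be combined to discover the influence on the primary results". For technique, "results will be compared between the combined groups 1 + 2 and 3 + 4"; for grafting, groups 1 + 3 are set against 2 + 4. Both contrasts are tested by unpaired t test. The reason given is to avoid interference arising from the presence of two main factors.

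The Sample size section supplies the planning values. It puts the effect of grafting at 0.8 mm and the within-group SD at 1 mm. For technique it expects that "the difference of the bone remodeling between the original TSFE groups and modified TSFE groups is around 0.5 mm".

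Residual bone height is an entry criterion ("The residual bone height of each participant is between 3 and 6 mm"). According to the Overview, a pre-operative CT "scan will be taken to assess the initial bone height, bone quality, and bone width". In the Statistical analysis section, residual bone height appears only as an example of a variable to be checked for agreement between examiners.

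**The concern.** An unpaired t test on pooled groups compares two sets of patients, each of which mixes grafted and non-grafted cases. If grafting shifts bone remodeling by 0.8 mm, that shift counts as random noise in the technique test. The method therefore works against its own stated purpose: collapsing hides the second factor in the residual, whereas a two-factor model would remove it.

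The cost falls on the technique comparison, which has the smaller planned effect and is already the weaker of the two. It also falls in an unhelpful direction. The article hopes to find the modified technique similar to the traditional one, and a noisier, conservative test makes a non-significant result more likely, which is easily misread as similarity.

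Pooling also summarises technique by a single number, which describes both grafting settings only if grafting acts alike under both techniques. No explicit check of this is stated.

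**Working it through.** **Inputs (Sample size section).** Grafting effect 0.8 mm; technique effect 0.5 mm; within-group SD 1 mm; α 0.05; 27 per group before losses and 30 recruited. Each side of a pooled contrast therefore has 54 (or 60) patients. The article does not say whether α is one- or two-sided; two-sided is assumed for the power figures below.

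**The plan's own figure.** n = 2(z_α + z_power)²σ²/δ² with δ = 0.8 and σ = 1.
- One-sided: 2 × 8.564 / 0.64 = 26.8, so 27 per group; 27 / 0.9 = 30; 4 × 30 = 120. This reproduces the article.
- Two-sided: 2 × 10.507 / 0.64 = 32.8, so 33 per group. This does not.

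**SD inside each pooled test.** In a balanced 2×2, leaving out a factor with effect d adds d²/4 to the variance.
- Technique test, grafting left out: √(1 + 0.8²/4) = √1.16 = 1.077.
- Grafting test, technique left out: √(1 + 0.5²/4) = √1.0625 = 1.031.

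**Power (noncentral t, two-sided 0.05).**

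| Comparison | Per side | Pooled t test | Both factors in the model |
|---|---|---|---|
| Technique, 0.5 mm | 54 | 66.7% | 73.0% |
| Technique, 0.5 mm | 60 | 71.3% | 77.5% |
| Grafting, 0.8 mm | 54 | 97.9% | 98.5% |

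A simulation of 5,000 balanced trials gave 67.3% for the pooled test and 72.2% for the two-factor model on technique.

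**Rejection when technique has no effect.** In balanced arms grafting cancels out of the technique difference, but the t test still divides by an SD of 1.077. The effective critical value is 1.983 × 1.077 = 2.135, giving a two-sided rejection rate of about 3.3%. Simulation gave 3.4%.

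**Bias.** With a true technique effect of 0.50 mm, the mean pooled estimate was 0.497 in balanced arms and 0.496 under simple, unblocked randomisation. Neither shows bias.

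**Adding residual bone height.** If r is its correlation with the outcome, the residual SD is √(1 − r²). The documents give no r, so these values are assumptions. At 54 per side, power for technique is 77.0% at r = 0.3, 80.2% at r = 0.4 and 84.4% at r = 0.5.

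**What the fix cannot do.** 90% two-sided power for 0.5 mm needs 2 × 10.507 / 0.25 = 84.1, so 85 per side at SD 1. At the pooled SD it needs 84.06 × 1.16 = 97.5, so 98. The trial has 54 to 60.

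**Precision of the interaction.** With 27 per cell, SE = √(4/27) = 0.385 mm. The 95% half-width is 1.983 × 0.385 = 0.76 mm, nearly as large as the planned grafting effect.

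**The case against.** Analysing a 2×2 factorial at its margins is a recognised approach, and here the test is valid and, in balanced arms, slightly conservative. For grafting, the effect that reproduces the stated sample size, the loss is trivial. The technique comparison is short of patients either way. All of this stands. It limits the size of the point, but it does not explain why a stated method should be kept when a better one is free.

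A reader might infer that pooling leaves the technique estimate confounded by grafting or by bone height. The documents do not support that. The factors are crossed by randomisation with equal arms planned, so the estimate is unbiased. Chance imbalance in the grafting share could move an individual estimate: under unblocked allocation, which the article neither states nor rules out, by an SD of about 0.07 mm. That is not a second harm. With 60 per side, grafting contributes 2 × (0.8/2)² / 60 = 0.0053 to the squared standard error, and the root of that is 0.073 mm. It is the same variance as in the power loss.

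Bias could arise from the removal, after allocation, of patients with a perforated membrane or an implant without initial stability. In one assumed scenario (30% perforation with osteotomes in the half with less bone, 5% otherwise, r = 0.5), the pooled estimate fell from 0.50 to 0.438 mm and adjustment returned 0.496. That is a separate question about the analysis population, and bone-height adjustment would in general answer it only in part.

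It is also fair to say that covariates are often left to an analysis plan, which is not shown here. Not naming bone height is therefore no error in itself; it enters only as part of a better model. Nor would an interaction be invisible: if the ANOVA covers the four arms, their means could partly reveal it.

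**Conclusion.** The point holds as one of efficiency. The pooled t tests leave the other factor in the error term, contrary to their stated aim. For technique this raises the SD from 1.00 to 1.077 and lowers power at 0.5 mm from about 73% to 67%; for grafting the loss is about half a point. These figures rest on the article's planning values, 54 per side and a two-sided 0.05 test.

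The pooled estimates are unbiased under randomisation, and no claim of confounding is made. Any gain beyond about 73% from bone height is conditional on an assumed correlation (77% to 84% for r = 0.3 to 0.5). The technique comparison stays below 90% power throughout that range.

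**What to change.** For each continuous primary outcome, replace the two pooled t tests by one linear model with technique, grafting and pre-operative residual bone height (continuous). State that this model is the primary analysis and takes precedence over the ANOVA. Report the adjusted technique and grafting differences with 95% confidence intervals, together with the four cell means. Report the technique-by-grafting term as descriptive only, given its half-width of about 0.76 mm.

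The cost is a change of wording in the Statistical analysis section. The bone-height measurement is already planned for all participants, and the planned software can fit the model. No extra patients or visits are needed.
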